### Study procedures [Table 1]

**Table 1 T1:** Schedule of events

	Screening	Enrollment	Baseline	1 week	3 weeks	6 weeks	3 months	6 months	12 months
				(3-10 d)	(11-28 d)	(4-8 we)	(11-15 we)	(5-7 mo)	(12-14 mo)
**Screening**	X								

**X-ray**	X		X (<24 h post-reduction)	X					X

**Informed Consent**		X							

**Randomization**		X							

**Baseline data**			X						

**Clinical follow-up**				X	X	X	X	X	X

**Revisision surgery**				X	X	X	X	X	X

**Complications**				X	X	X	X	X	X

**Pain (VAS)**				X	X	X	X	X	X

***Quick-*DASH**						X	X	X	X

**MEPI**						X	X	X	X

**Oxford Elbow Score**						X	X	X	X

**SF-36**						X	X	X	X

**EQ-5D**						X	X	X	X

**Health care consumption**						X	X	X	X

**ROM**						X	X	X	X

**Early withdrawal**				*	*	*	*	*	*

*, only if applicable

Clinical assessments will occur at the time of admission (baseline), one week (3-10-day window), three weeks (11-28-day window), six weeks (4-8-week window), three months (11-15-week window), six months (5-7-month window), and 12 months (12-14-month window) after start of treatment.

At each FU visit, the research coordinator or research assistant will ascertain patient status (i.e., secondary interventions, adverse events/complications, deaths) and will verify information within medical records.

At each FU visit, the patients will be asked to indicate the pain level on a VAS.

At each visit from six weeks onwards, the ROM of the elbow will be measured using a goniometer by a doctor blinded for the treatment of the dislocation. This will be used to calculate the MEPI index. In addition, patients will be asked to complete the questionnaires relating to disability (*Quick-*DASH score including optional modules, Oxford Elbow Score), health-related quality of life (SF-36, EQ-5D), and healthcare consumption.

Plain X-rays of the elbow will be made at the time of presentation in the hospital (baseline), post-reduction, and at the follow-up visit after one week and one year. The X-ray at 12 months will be taken in order to determine the amount and location of heterotopic ossification and the grade of degenerative joint changes. This is common practice in this type of patient. At the last visit, the surgeon will document any surgery that may be planned for the patient.

### Sample size calculation

Calculation of the required sample size is based upon the assumption that the mean *Quick-*DASH will be 12.5 in plaster treated patients and five in the functional group, assuming a standard deviation of 15 for the plaster group and 7.5 for the functional group [7]. A 2-sided test with an α level of 0.05 and a β level of 0.2 requires 41 patients in each group. Anticipating a dropout rate of 20% loss to follow-up a sample size of 50 patients in each arm is required.

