**Methods/Design:**

The design of the study will be a multicenter randomized controlled trial of 100 patients who have sustained a simple elbow dislocation. After reduction of the dislocation, patients are randomized between a pressure bandage for 5-7 days and early functional treatment or a plaster in 90 degrees flexion, neutral position for pro-supination for a period of three weeks. In the functional group, treatment is started with early active motion within the limits of pain. Function, pain, and radiographic recovery will be evaluated at regular intervals over the subsequent 12 months. The primary outcome measure is the *Quick *Disabilities of the Arm, Shoulder, and Hand score. The secondary outcome measures are the Mayo Elbow Performance Index, Oxford elbow score, pain level at both sides, range of motion of the elbow joint at both sides, rate of secondary interventions and complication rates in both groups (secondary dislocation, instability, relaxation), health-related quality of life (Short-Form 36 and EuroQol-5D), radiographic appearance of the elbow joint (degenerative changes and heterotopic ossifications), costs, and cost-effectiveness.

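### The sample-size figures do not agree: 41 evaluable per group with 20% loss needs 52 randomised per arm, not 50; the effect on power is negligible

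*Protocol article*

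**What the plan says.** The Sample size calculation section assumes mean Quick-DASH scores of "12.5 in plaster treated patients and five in the functional group". The spread is set separately for each arm: "assuming a standard deviation of 15 for the plaster group and 7.5 for the functional group". From these it concludes: "A 2-sided test with an α level of 0.05 and a β level of 0.2 requires 41 patients in each group". The next sentence makes the allowance for attrition: "Anticipating a dropout rate of 20% loss to follow-up a sample size of 50 patients in each arm is required". The Methods/Design part of the abstract carries the resulting total, describing a "multicenter randomized controlled trial of 100 patients who have sustained a simple elbow dislocation".

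The Statistical analysis section names Student's t-test for continuous outcomes judged parametric and the Mann-Whitney U-test otherwise. The article gives no inflation formula and attaches no other meaning to the 20%.

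**The concern.** Two consecutive sentences give three figures: 41 needed, 20% lost, 50 randomised. One multiplication shows that they disagree, because 80% of 50 is 40. If attrition runs exactly as anticipated, each arm finishes one patient below the number the plan says it requires.

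What is at stake is mainly the accuracy of the stated justification. Ethics committees and readers rely on this paragraph to judge whether the trial is large enough, and it credits 50 per arm with covering more loss than it does. A shortfall in the evaluable number could also mean lost power, so its size has to be checked.

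**Working it through.** **Inputs** (Sample size calculation section): means 12.5 and 5, so a difference of 7.5; standard deviations 15 and 7.5; two-sided alpha 0.05; beta 0.2, so power 0.80; anticipated loss 20%; equal arms of 50.

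**Step 1. Reproduce the 41.**

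Normal approximation:

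n = (1.96 + 0.842)² × (15² + 7.5²) / 7.5² = 7.85 × 281.25 / 56.25 = 39.2, so 40 per group.

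The t-test needs slightly more. Power from the noncentral t distribution, with noncentrality 7.5 / √(281.25/n):

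| Evaluable per group | Student's t | Welch | Normal approximation |
|---|---|---|---|
| 40 | 79.8% | 79.4% | 80.7% |
| 41 | 80.8% | 80.4% | 81.7% |

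By either t-test, 41 is the smallest number that reaches 80%. The stated 41 is therefore reproduced.

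**Step 2. Allow for 20% loss.**

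If a fraction d of those randomised is lost, N randomised leave N(1 − d) evaluable, so N = n/(1 − d):

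- 41 / (1 − 0.20) = 51.25, so 52 per arm and 104 in total.
- Check: 52 × 0.80 = 41.6, and 51 × 0.80 = 40.8, so 51 is not quite enough.

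**Step 3. What 50 per arm delivers.**

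- At 20% loss: 50 × 0.80 = 40 per arm, one below 41.
- Largest loss that keeps 41: 1 − 41/50 = 18%.
- Power at 40 per arm (table above): 0.2 percentage points below 80% by Student's t, 0.6 points below by Welch.

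**Step 4. Where 50 might have come from.**

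41 × 1.20 = 49.2, which rounds up to 50. The stated figure is consistent with multiplying by 1.2 instead of dividing by 0.8. It is equally consistent with 51.25 having been taken down to a convenient 50 per arm, 100 in total. The article does not settle which.

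**The case against.** **The size.** The strongest objection is that this hardly matters. Under the t-test the plan names, 79.8% rounds to the planned 80%. The shortfall is one evaluable patient per arm, smaller than the uncertainty in the assumptions. Raising the plaster standard deviation from 15 to 15.2 already moves the Student's t requirement from 41 to 42, and 15.5 moves it to 43. The 20% is itself a forecast. All of this stands, and it is why the point is minor. It does not make the printed figures agree.

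**The method.** The normal approximation needs only 40 evaluable patients, and 40/0.80 = 50 exactly, with 80.7% power. So a standard method exists under which 50 per arm, 20% loss and 80% power hold together. A reader might infer from the mismatch that the stated size, loss rate and power are incompatible; the documents do not support that. The conflict is narrower, between the printed 41, the 20% and the 50. The objection does not remove that conflict, because the article states 41, which is the t-test answer. If 40 was meant, the 41 is the figure to correct.

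**The cause.** A reader might also take it as established that the dropout step multiplied by 1.2. That is inference, since no formula is shown.

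**The format.** A journal article condenses a longer protocol. That would excuse an omission, but here both figures are printed and they disagree.

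**Conclusion.** The point holds as a minor arithmetic inconsistency. With 41 evaluable patients required per group and 20% loss, 52 per arm (104 in total) must be randomised. The stated 50 per arm (100 in total) leaves 40 and tolerates 18% loss. The gap is one evaluable or two randomised patients per arm, four randomised in total.

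The loss of power is negligible: 79.8% by Student's t-test or 79.4% by Welch, against 80%. A reader might infer that the trial is underpowered; these figures do not support that reading. Nor would it be fair to give the power as about 79% without qualification, since that rests on Welch, whereas the plan names Student's t-test.

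The mismatch itself depends on no choice of method: it needs only the printed 41, 20% and 50, with the 20% read as a share of those randomised. The power figures rest on the plan's assumed means and standard deviations, normally distributed scores, equal arms and equal loss in both arms.

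**What to change.** Keep 100 patients and replace the dropout sentence in the Sample size calculation section with wording such as:

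*Fifty patients per arm allows 18% loss to follow-up while retaining 41 evaluable per group; at 20% loss, 40 per arm remain and power is just under 80% (79.8%, Student's t-test).*

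This costs one sentence and no extra patients, and it leaves the design and the analysis unchanged. The only price is that the stated attrition allowance becomes slightly less favourable. If the sponsor prefers to keep both the 41 and the 20%, the target becomes 52 per arm, 104 in total. That is four more patients, which the small difference in power hardly demands.

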### Statistical analysis

Data will be analyzed using the PASW Statistics version 18.0.1 or higher (SPSS, Chicago, Illinois, USA). Normality of continuous data will be tested with the Shapiro-Wilk and Kolmogorov-Smirnov test and by inspecting the frequency distributions (histograms). The homogeneity of variances will be tested using the Levene's test.

The analysis will be performed on an intention to treat basis. Patients with protocol violations will be followed up, and data will be recorded. Data will be analyzed with and without inclusion of patients with protocol violation.

Descriptive analysis will be performed to report baseline characteristics (intrinsic variables and injury-related variables) in both treatment groups. For continuous data (e.g., age, Quick-DASH score at baseline) mean ± SD (parametric data) or medians and percentiles (non-parametric data) will be calculated. For categorical data (e.g., gender, ASA grade, alcohol and tobacco consumption, dominant and affected side) frequencies will be calculated.

The mean difference between the mean *Quick-*DASH scores of the functional group and the plaster group will be tested. Univariate analysis will be performed to test the difference in the primary and secondary outcome measures between the functional and the plaster groups. Continuous data will be tested using a Student's T-test (parametric data) or a Mann Whitney *U*-test (non-parametric data). Chi-square analysis will be used for statistical testing of categorical data. A p-value <0.05 will be taken as the threshold of statistical significance.

A multivariable linear regression analysis will be performed to model the relationship between different covariates and the *Quick-*DASH score. Intrinsic and injury-related variables that display a p-value <0.5 in the univariate analyses will be added as a covariate.

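### With four scheduled Quick-DASH visits and 20% loss expected, the named single-visit tests ignore the earlier scores of patients lost later; a repeated-measures model would be more robust

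*Protocol article*

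**What the plan says.** All references are to the protocol article.

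- **Analysis basis** (Statistical analysis): "The analysis will be performed on an intention to treat basis". The sentences that follow explain this for protocol violators only. They stay in follow-up, and "Data will be analyzed with and without inclusion of patients with protocol violation".
- **Tests** (Statistical analysis): continuous outcomes, including the primary Quick-DASH, are compared by a Student's "T-test (parametric data) or a Mann Whitney *U*-test (non-parametric data"). A multivariable linear regression is added, with covariates drawn from the intrinsic and injury-related variables. Quick-DASH scores from earlier visits are not among them.
- **Expected loss** (Sample size calculation): "A 2-sided test with an α level of 0.05 and a β level of 0.2 requires 41 patients in each group", and then "Anticipating a dropout rate of 20% loss to follow-up a sample size of 50 patients in each arm is required".
- **Schedule** (Table 1): Quick-DASH at six weeks, three months, six months and 12 months.
- **Blinding** (Recruitment and consent): surgeons and patients know the allocated treatment.

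The article names no method for missing scores and writes no rule that patients without a score are left out. The two statistical sections do not say which visit carries the primary comparison.

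**The concern.** A two-sample test at one visit uses one number per patient. A patient with no score at that visit adds nothing, even with one, two or three Quick-DASH scores already on file. With 50 per arm and 20% loss at the tested visit, that is about 10 patients per arm, 20 of 100.

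The resulting estimate is safe if loss is unrelated to outcome. Here the arms are unblinded and differ in early management and contact: under Intervention, physical therapy begins after two days in one arm and after three weeks of plaster in the other. It is plausible, though the article gives no data on it, that staying in follow-up depends on how recovery is going, and not equally in both arms. If so, the difference among patients with scores is no longer the difference among those randomised, and it can be wrong in either direction. The scheduled earlier scores carry information about this, and the named tests leave it unused.

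**Working it through.** **1. The plan's own figures.** Inputs from Sample size calculation: means 12.5 and 5, so a difference of 7.5; SDs 15 and 7.5; two-sided α 0.05; power 80%.

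- Root-mean-square SD = √[(15² + 7.5²)/2] = √140.6 = 11.86.
- Normal approximation: n = 2 × 11.86² × (1.960 + 0.842)² / 7.5² = 39.2, so 40 per arm.
- Noncentral t: 41 per arm gives 80.8% power and 40 gives 79.8%. The stated 41 is reproduced.
- With 20% loss, 50 × 0.8 = 40 scores per arm, so about 80% power remains.

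The power statement thus already refers to patients with scores, not to all 100 randomised. Loss of power is not the issue.

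**2. Effect of score-dependent loss on a visit-wise comparison.** The article gives no dropout pattern, so these are assumptions: planning means and SDs at both six and 12 months; bivariate normal scores; correlation ρ of 0.5 or 0.7 between the visits; 35% loss on one side of the arm's six-month mean and 5% on the other, which is 20% overall.

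- Retained shares are 0.65 and 0.95. Mean distance from the centre of each half of a normal distribution is √(2/π) = 0.798 SD.
- Shift in the completers' six-month mean = 0.798 × (0.95 − 0.65)/(0.95 + 0.65) = 0.1496 SD.
- Shift at 12 months = 0.1496 × ρ × SD.

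| Who leaves | Shift in the difference | ρ = 0.5 | ρ = 0.7 |
|---|---|---|---|
| Recovered patients, both arms | +0.1496 ρ (15 − 7.5) | 8.06 | 8.29 |
| Poorly recovered in plaster, recovered in functional | −0.1496 ρ (15 + 7.5) | 5.82 | 5.14 |
| Recovered in plaster, poorly recovered in functional | +0.1496 ρ (15 + 7.5) | 9.18 | 9.86 |

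The true value is 7.5 throughout. Simulation with 50 per arm gave 8.0 to 8.3 for the first row, 5.2 to 5.9 for the second and 9.3 to 9.8 for the third, which agrees with the formula to about 0.1 point. A likelihood-based estimate using the six-month score within each arm gave about 7.5 in every row. The first row shows bias despite the same loss rule in both arms only because the planning SDs differ.

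**3. Scale.** The standard error with 40 per arm is √(15²/40 + 7.5²/40) = 2.65. A shift of 0.6 to 0.8 is under a third of that. The opposite-direction shifts of 1.7 to 2.4 (0.1496 × ρ × 22.5) are about 0.6 to 0.9 of it.

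**4. Precision under random loss.** If every lost patient has an earlier score, the variance of the arm mean falls by the factor 1 − 0.2ρ². For ρ = 0.5 this is 0.950, and for ρ = 0.7 it is 0.902. The standard errors fall by 2.5% and 5.0%. The simulations gave 1 to 5%.

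**The case against.** - **The article is silent on missing data, and the full protocol or SAP may cover it.** This stands as far as it goes. No complete-case rule is written, and a t-test can be run on imputed data. The point made here is narrower. It concerns the method the article does choose: single-visit tests for an outcome measured four times, with substantial loss anticipated.
- **A reader might infer that the plan breaks its own intention-to-treat promise.** The document does not support that. It explains the term as keeping protocol violators in the analysis, and comparing patients by allocated arm is consistent with that. Nor would the model proposed here include every randomised patient. The first Quick-DASH is at six weeks, so anyone lost sooner contributes nothing to it either.
- **A reader might infer that the collected data would remove the bias.** That is too strong. In the simulation, loss was generated from the six-month score alone, so a method that conditions on that score recovers 7.5 by construction. If loss depends on status that was never recorded, some bias stays.
- **The size depends on the scenario.** This stands. The 35% against 5% gradient is assumed, and no reason in the article makes opposite-direction loss likely. In the milder scenario the bias is 0.6 to 0.8 points. The timing of loss is not given, so how many lost patients would have an earlier score is unknown. Exclusion 9 (likely problems with follow-up) may lessen the loss. Normal scores with mean 5 and SD 7.5 also put about a quarter of simulated functional-arm values below zero, which the 0 to 100 scale does not allow.

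**Conclusion.** The point holds as a weakness in the choice of primary method, not as a contradiction in the text. The article fixes tests that use one visit at a time while it schedules four and expects a fifth of patients to be lost. If loss tracks earlier recovery, the visit-wise difference is less robust than one that uses all scheduled scores.

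Under the assumed patterns, a true 7.5 becomes about 8.0 to 8.3 in the milder case and lies between about 5.2 and 9.8 when loss runs in opposite directions by arm. These figures rest on assumed gradients, assumed correlations and missing at random. They show what could happen and do not predict it. If loss is random, the visit-wise test is unbiased and the gain is only 1 to 5% in standard error. The recommendation is worth adopting because it is cheap, with medium confidence in how much it will matter.

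**What to change.** - **Primary analysis:** one linear mixed model for Quick-DASH at all four visits, with treatment, visit and treatment-by-visit terms and all randomised patients who have at least one score. Use an unstructured covariance that may differ by arm, because the article plans for "a standard deviation of 15 for the plaster group and 7.5 for the functional group". With these terms the model is equivalent to fitting each arm separately and subtracting the visit means, should the chosen software version not allow arm-specific covariance.
- **Contrast:** read the treatment difference at one prespecified visit, named in the plan.
- **Earlier scores:** enter them as outcomes, not as covariates in the planned regression, because they are all measured after treatment has started.
- **Sensitivity analyses:** keep the visit-wise t-test or Mann-Whitney test, and check robustness to skewed scores.

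**Cost:** a change of wording and a little more analysis work, with no extra patients or visits. **Downsides:** reliance on missing at random, the need for the skewness check, and no contribution from patients lost before six weeks.

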### Study population

All persons aged 18 years or older presenting with a simple elbow dislocation at the Emergency Departments of the participating clinics are eligible for inclusion.

Patients meeting the following inclusion criteria are eligible for enrolment:

1. Adult men or women aged 18 years and older (with no upper age limit)

2. A simple dislocation of the elbow (i.e., without associated fracture) that can be reduced by closed means. Presence of a dislocation and absence of fracture(s) will be confirmed by a plain X-ray

3. Provision of informed consent by patient

If any of the following criteria applies, patients will be excluded:

1. Polytraumatized patients

2. Patients with complex, pathological, recurrent or open dislocations

3. Additional traumatic injuries of the affected arm

4. Patients undergoing surgical repair of collateral ligaments of the dislocated elbow joint

5. Patients with an impaired elbow function (i.e., stiff or painful elbow or neurological disorder of the upper limb) prior to the injury

6. Retained hardware around the affected elbow

7. History of operations or fractures involving the elbow

8. Patients with rheumatoid arthritis

9. Likely problems, in the judgment of the investigators, with maintaining follow-up (e.g., patients with no fixed address)

10. Insufficient comprehension of the Dutch language to understand a rehabilitation program and other treatment information, which will be judged by the attending physician

Exclusion of a patient because of enrolment in another ongoing drug or surgical intervention trial will be left to the discretion of the attending surgeon on a case-by-case basis.

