Radiographic appearance (anteroposterior and lateral X-ray at one year): heterotopic ossification will be classified according the classification scheme of Broberg and Morrey as a bone exostosis or as a soft tissue ossification of a ligament, capsule or muscle ("myositis ossificans") [23]; degenerative changes will be classified as grade zero (no change), grade 1 (slight narrowing of the joint space with small osteophytes), grade 2 (moderate narrowing of the joint space, osteophytes and subchondral sclerosis), and grade 3 (severe narrowing of the joint space, large osteophytes, subchondral sclerosis and cystic deformation).

The incremental cost-effectiveness ratio of functional versus plaster treatment will be expressed in a cost-utility ratio, i.e., in terms of cost per QALY. The economic evaluation will be performed from a societal perspective, and will include both health care costs and costs of production losses. Health care costs will include costs of general practice care, medical specialist care, physical therapy, hospitalization, medication, and other costs directly associated with diagnosis, treatment and rehabilitation. Patients will be asked to administer a custom-made questionnaire to register their health care needs and production loss.

In addition to the outcome variables mentioned above, the following data will be collected:

a) Intrinsic variables (baseline data): age, gender, American Society of Anesthesiologists' ASA classification, tobacco consumption, alcohol consumption, comorbidity, social status/household composition, dominant side, and medication use.

b) Injury related variables: affected side, mechanism of injury, and assessment of varus, valgus and posterolateral rotatory instability.

c) Intervention-related variables: reduction delay (i.e., time between dislocation and reduction), time between injury and start of physical therapy, days of sling use, and number of physical therapy sessions

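### SF-36 and EQ-5D are compared only by unadjusted tests although prognostic covariates are recorded; prespecified adjustment could give a small gain in precision (optional)

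*Protocol article*

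**What the plan says.** All places are in the protocol article.

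- **Test for these outcomes.** Statistical analysis: "Univariate analysis will be performed to test the difference in the primary and secondary outcome measures between the functional and the plaster groups". For continuous data this means a Student's t-test or a Mann-Whitney U-test, and neither takes covariates.
- **Scope of the covariate model.** Same section: "A multivariable linear regression analysis will be performed to model the relationship between different covariates and the" Quick-DASH score. No other outcome is named for it.
- **Covariates in hand.** Outcome measures, item a: "Intrinsic variables (baseline data): age, gender, American Society of Anesthesiologists' ASA classification, tobacco consumption, alcohol consumption, comorbidity", among others.
- **Timing of the scores.** Table 1 marks SF-36 and EQ-5D at six weeks and at 3, 6 and 12 months, with no mark at baseline. The text under Study procedures agrees. It ties the questionnaires to visits from six weeks onwards, beginning "In addition, patients will be asked to complete the questionnaires relating to disability", and goes on to list SF-36 and EQ-5D.
- **Who is enrolled.** Study population: "Adult men or women aged 18 years and older (with no upper age limit". Rheumatoid arthritis, polytrauma and earlier elbow problems are excluded; general comorbidity is not.
- **Status of the outcomes.** Health-related quality of life is listed among the secondary aims at the end of the Background.

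**The concern.** SF-36 and EQ-5D measure general health, so they plausibly vary with age and other illness as well as with the state of the elbow. In a group of adults without an upper age limit, part of the spread in follow-up scores will have nothing to do with the injury. A baseline score would usually remove some of that spread, but none is scheduled. The recorded covariates are then the only means already in the plan of doing so, and the stated comparison of these outcomes leaves them out. The plan does model covariates for the elbow-related Quick-DASH, where general health plausibly matters less.

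At stake is the width of the confidence intervals for a stated secondary aim: a real quality-of-life difference is somewhat easier to miss than it need be.

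**Working it through.** **1. The plan's own sample size, to fix the number analysed.** The Sample size calculation section assumes that the average score "will be 12.5 in plaster treated patients and five in the functional group". Its SDs are 15 (plaster) and 7.5 (functional). The root-mean-square SD is sqrt((15² + 7.5²)/2) = 11.86. For a difference of 7.5 and a two-sided 5% test, the noncentral t gives power 0.798 at 40 per arm and 0.808 at 41. The statement "A 2-sided test with an α level of 0.05 and a β level of 0.2 requires 41 patients in each group" is reproduced. The plan then recruits 50 per arm and allows for 20% loss, so 50 × 0.8 = 40 per arm are expected at analysis. This calculation concerns the Quick-DASH; the article states no sample size or power for SF-36 or EQ-5D.

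**2. Inputs for the SF-36 illustration.**
- SD 10 for a component score. This is the norm-based SD for the US general population given under Outcome measures; using it for trial patients is an assumption.
- n = 40 per arm, N = 80 in total (step 1).
- A 5-point difference, as an illustration only; the article gives no target.
- R², the share of score variance explained by age, gender, ASA class and comorbidity. The article gives none; the range taken is 0.05 to 0.30.
- k = 4 covariate terms, one for each covariate.

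**3. Unadjusted comparison.** SE = 10 × sqrt(2/40) = 2.24 points. Power for 5 points (noncentral t, 78 df) = 0.60.

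**4. Adjusted comparison.** Adjustment multiplies the variance by (1 − R²). Estimating the covariate effects multiplies the expected variance by (N − 3)/(N − k − 3) = 77/73 = 1.055. So

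SE = 2.236 × sqrt((1 − R²) × 77/73),

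and the equivalent unadjusted sample is 40 / ((1 − R²) × 77/73) per arm.

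| Assumed R² | (1 − R²) × 77/73 | SE (points) | Power for 5 points | Equivalent n per arm |
|---|---|---|---|---|
| unadjusted | 1 | 2.24 | 0.60 | 40 |
| 0.05 | 1.002 | 2.24 | 0.60 | 40 |
| 0.10 | 0.949 | 2.18 | 0.62 | 42 |
| 0.20 | 0.844 | 2.05 | 0.67 | 47 |
| 0.30 | 0.738 | 1.92 | 0.73 | 54 |

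Break-even is at R² = 1 − 73/77 = 0.052. Below that, adjustment costs slightly more than it returns.

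**5. Sensitivity to coding.** If ASA class and comorbidity each took two terms, k = 6 and the factor is 77/71 = 1.085. The SE is then 2.27 at R² = 0.05, slightly worse than unadjusted, and 2.21 at R² = 0.10. Break-even rises to 1 − 71/77 = 0.078. The covariate set has to stay small.

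**6. Chance imbalance.** The chance that the arms differ by at least 0.3 SD on any one covariate is 2 × (1 − Φ(0.3/sqrt(2/40))) = 2 × (1 − Φ(1.34)) = 0.18. At an assumed correlation of 0.4 with the score, a 0.3 SD imbalance moves the difference by 0.4 × 0.3 × 10 = 1.2 points, or 1.2/2.24 = 0.54 SE. This is not an extra error. The unadjusted variance is 10² × 2/40 = 5.0, and at correlation 0.4 the share 0.16 × 5.0 = 0.8 of it is this covariate's imbalance. The interval from step 3 already covers it.

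**7. EQ-5D.** The article gives no SD, so no SE in points can be computed. The relative change in variance (second column of the table) applies for the same R².

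**The case against.** The strongest reply is that nothing here is wrong. An unadjusted t-test or Mann-Whitney test is valid in a randomised trial, one rule for all continuous secondary outcomes is ordinary practice, and adjustment is a matter of efficiency. That stands, and it limits the point to an improvement. The reply also holds that a condensed article may leave further models to the full plan. That has less force: the article does state the test for these outcomes, and a stated method can be improved. It does not, however, rule out adjusted analyses elsewhere.

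Second, the gain depends on an R² that nobody has stated, and estimating four effects in 80 patients is not free. This stands too: at R² of about 0.05 the gain disappears. The exclusions of polytrauma, rheumatoid arthritis and prior elbow problems may also narrow the spread of general health.

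Three stronger readings are tempting, and the article supports none of them.

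- *That chance imbalance in age or comorbidity biases the quality-of-life result.* Randomisation excludes systematic bias, and the unadjusted SE already contains the imbalance (step 6).
- *That the missing baseline score is itself the fault.* Patients are recruited in the emergency department after an acute dislocation, so a true pre-injury score cannot be collected prospectively. Its absence only explains why the recorded covariates are worth using.
- *That the cost-utility result is affected through EQ-5D.* The article speaks of cost per QALY but does not name the source of the utilities, so the link is an inference.

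**Conclusion.** The point holds as a minor one. The stated comparison of SF-36 and EQ-5D ignores covariates that the trial records, and no baseline score does their work. The consequence is some avoidable loss of precision on secondary outcomes, with no bias and no effect on the Quick-DASH conclusion.

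With four terms, the SE reduction runs from nothing at R² = 0.05 to about 14% at R² = 0.30 (1.92/2.24 = 0.86), worth between 0 and 14 patients per arm. These figures rest on the assumed SD of 10, 40 evaluable patients per arm and the assumed R² range. A reader might take the 0.60 power for 5 points as a shortfall. It is not one: the trial was sized for the Quick-DASH alone, and the 5 points are only illustrative.

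**What to change.** In the Statistical analysis section, add that the SF-36 component scores and EQ-5D will be analysed by linear regression on treatment arm plus age, gender, ASA class and comorbidity. Code ASA class and comorbidity as one term each. Fix the set in advance, with no selection by p-value, and use robust or bootstrap standard errors if the scores are skewed. Report the adjusted mean difference with its 95% confidence interval beside the unadjusted result.

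The cost is a few lines of text, four degrees of freedom out of 78 and one extra model per outcome. No new data, visits or patients are needed. The downside is little or no gain if the covariates explain only about 5% of the variance, and a slight loss below that.
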